#### 2.5.2. Secondary Outcomes

The secondary outcomes included objectively measured changes in MVPA, immediately after the intervention; changes in steps, light PA (LPA), sedentary behaviour, and proportion of engagement in the recommended hour of PA (60 min) per day; changes in self-reported MVPA and sedentary behaviour; mental and social health variables immediately and at six months post-intervention; changes in the above variables in subgroups of children disliking exercise or in a being precontemplation stage of the transtheoretical model of behaviour change.

### 2.6. Data Collection

Objectively measured PA and questionnaire data were collected at four time-points: at baseline; a four-week follow-up (mid-intervention); a 6-month follow-up (immediately post-intervention); and a one-year follow-up (six-month post-intervention). Bone mass data were collected at two time-points: during September 2018 as a baseline measure and during September 2019 as a follow-up measure; both collections coincided with the health check-up routinely conducted at the beginning of the second semester (Table 1).

#### 2.6.1. Objectively-Measured Physical Activity

Objectively measured PA was evaluated by Fitbit Ace (Fitbit, Inc., San Francisco, CA, USA), a wrist-worn activity tracker for children aged eight years and older. It features a tri-axial accelerometer and continuously acquires data. It has onboard storage capacity for approximately five days of data without syncing. Participants were asked to wear the device on the non-dominant wrist for 24 h and for 10 days during each of the four time-points, except while bathing, swimming, or playing sports with a high risk of injury. Additionally, participants were asked to charge the Fitbit Ace’s battery during the first period in the classroom every day. Moreover, using Bluetooth technology, the investigators synced the Fitbit’s mobile app data to a Fitbit server two or three times (every third or fourth day) during the 10 days of each period. These collected data from Fitbit Ace devices were downloadable via an application programme interface (API), and the data collected at 1 min intervals provided information on step counts and the time spent in the following activity levels: sleep, sedentary, light, fairly (or moderately) active, and very active/vigorous). Although the Fitbit Ace device has not been established as a valid objective measure of PA yet, similar wrist-worn Fitbit devices (Fitbit Flex2, Fitbit, Inc., San Francisco, CA, USA) have shown excellent correlations between step counts and ActiGraph GT3X+ (ActiGraph, Pensacola, USA), the most valid and widely used tool to measure PA in research [25]. Fitbit Charge HR (Fitbit, Inc., San Francisco, CA, USA) also has adequate sensitivity in classifying moderate and vigorous activity and sleep [26].

#### 2.6.2. Self-Reported Physical Activity and Sedentary Behaviour

Self-reported PA was measured using the following three questions used in the Health Behaviour in School-Aged Children study: (1) Number of days with MVPA ≥60 min (days/week); (2) frequency of VPA (days/week); and (3) duration of VPA (hours/week) [27]. The validity and reliability of these items are acceptable among children [28].

Sedentary behaviour, such as screen time while watching TV or DVDs, video gaming, and using smartphones and PCs, etc., were measured separately on weekdays and holidays. Additionally, data regarding PA-related variables, such as participation in organised sports and active school transportation, were collected.

#### 2.6.3. Bone Mass

A bone mass survey for children in elementary schools from grade 4 to junior high school grade 3 (aged 9–15 years) has been conducted every August and September since 2006 as part of the Project Koshu. Bone stiffness was assessed as an indicator of bone mass using quantitative ultrasound (QUS). QUS measurements were performed with an Achilles A-1000 Express II (GE Healthcare, Milwaukee, WI, USA). This portable device measures bone stiffness using ultrasound waves and presents three parameters: (1) broadband ultrasound attenuation (BUA) which reflects the absorption of sound waves (dB/MHz); (2) SOS which expresses the stiffness of a material using the ratio of the traversed distance to the transit time (m/s); (3) stiffness index (SI) which is an automatically calculated parameter that combines BUA and SOS values [SI = (0.667 × BUA) + (0.278 × SOS) − 417]. The SI of the right foot calcaneus was used as the bone mass parameter in this study. To equalise the measurement conditions, setup was completed 20 min before the start of measurement for children; the room temperature at the time of measurement in each school was controlled at 25–27 °C, calibration was performed, and the stability of the measurements were confirmed.

#### 2.6.4. Bone Mass-Related Measures

Age in months, body composition measurements (body height, weight, and body mass index), calcium intake, puberty status, and socioeconomic status were identified as bone mass-related measures. Detailed evaluation for these variables is previously described [29].

#### 2.6.5. Mental Health

As an index of mental health, the rate of depressive symptoms evaluated by the Japanese-translated version of Birleson Depression Self-Rating Scale for Children (DSRS-C) [30,31], which is a valid and reliable tool. The questionnaire was obtained from another survey conducted every July annually under Project Koshu. DSRS-C consists of 18 questions with responses including ‘most’, ‘sometimes’, and ‘never’ scored as 2, 1, and 0, respectively. The total score was calculated as the DSRS-C score. Based on previous studies, a score of 16 or higher indicated depressive symptoms. The evaluation in July 2018 was used as the baseline data, and the evaluation in July 2019 was used as the post-intervention follow-up result.

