### 2.10. Statistical Analysis

For inter-group comparisons of characteristics at baseline, independent t-tests and chi-square tests will be used for continuous and categorical variables, respectively. Missing values will be complemented using the multiple imputation method, which is integrated using Rubin’s formula [42], by creating 20 datasets under the assumption of the missing measurement mechanism of missing at random (intention-to-treat). To evaluate the effect of the intervention programme, a general linear mixed model will be employed for the analysis of continuous variables. Sensitivity analysis will be conducted for complete case analysis excluding data with missing values. Regarding the analysis of dichotomous secondary outcomes, the intervention effect will be examined by comparing the odds ratio estimated using multi-level (logistic model) regression analysis. Additionally, subgroup analysis will be performed in the population disliking exercise or precontemplation stage of transtheoretical model of behaviour change. All statistical analyses will be performed using Stata SE version 15.1 (StataCorp, Spring, TX, USA).

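### The only named mental-health index is the proportion with DSRS-C scores of 16 or more; the total score is already calculated and would estimate the effect more precisely

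*Protocol article*

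**What the plan says.** Section 2.6.5 (Mental Health) names one measure: "As an index of mental health, the rate of depressive symptoms", assessed with the DSRS-C. The scale has 18 items scored 0, 1 or 2, so the total runs from 0 to 36. The section adds "The total score was calculated as the DSRS-C score" and, citing previous studies, "a score of 16 or higher indicated depressive symptoms". On timing, "The evaluation in July 2018 was used as the baseline data", and July 2019 supplies the follow-up.

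The introduction gives depressive symptoms as the mental factor, and Table 1 lists only the DSRS-C under mental health. Section 2.5.2 places the measure among the secondary outcomes, within "mental and social health variables immediately and at six months post-intervention".

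Section 2.10 has two routes. For continuous outcomes, "a general linear mixed model will be employed for the analysis of continuous variables". For dichotomous secondary outcomes, "the intervention effect will be examined by comparing the odds ratio estimated using multi-level (logistic model) regression analysis". It does not name the DSRS-C under either. A rate is dichotomous, so the logistic route is the natural reading, but it is an inference.

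**The concern.** A yes/no outcome treats a child who moves from 30 to 17 as unchanged, and a child who moves from 16 to 15 as recovered. If the programme shifts scores modestly across the range, most of that shift never crosses 16 and the odds ratio does not see it.

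The trial has nine schools, so it has little precision to spare. Other scales in the article are kept as scores: grit as an average, school connectedness and personality traits as sums. The sole mental-health measure is the one defined by a cut, and the only support given is that earlier studies used the threshold. At stake is the precision of one secondary comparison.

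**Working it through.** **The plan's own figures (section 2.7).** With d = 0.50, two-sided alpha 0.05 and power 0.80, n = 2 × (1.96 + 0.84)² / 0.50² = 62.7, or 63 per group, as stated. The design effect is 1 + 19 × 0.05 = 1.95, and 63 × 1.95 × 2 = 245.7, or 246, as stated. Dividing 246 by 0.7 × 0.9 × 0.9 gives 433.9, against 433 stated.

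**Children available.** The article gives no analysed headcount. Applying its acceptance and drop-out rates to the 511 children gives 511 × 0.7 × 0.9 × 0.9 = 289.7. I take 290, or 290 / 9 = 32.2 per school. This is implied, not stated.

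**Prevalence of scores of 16 or more.** Not in the article. Assumed 10%, 20% and 30%.

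**Step 1: independent children.** For a normal score and a shift in its mean, a cut at prevalence p keeps φ(z_p)² / [p(1 − p)] of the information.

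| Assumed p | φ(z_p) | Kept | Lost |
|---|---|---|---|
| 10% | 0.1755 | 0.34 | 66% |
| 20% | 0.2800 | 0.49 | 51% |
| 30% | 0.3477 | 0.58 | 42% |
| 50% | 0.3989 | 0.64 | 36% |

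The maximum, 0.64, is at 50%. The loss reaches one half at about 21% prevalence and below.

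**Step 2: clustering.** I use the protocol's ICC of 0.05 for the score and assume 0.03 for the cut.
- Design effect for the score: 1 + 31.2 × 0.05 = 2.56.
- Design effect for the cut: 1 + 31.2 × 0.03 = 1.94.
- Ratio: 2.56 / 1.94 = 1.32.
- Kept: 0.342 × 1.32 = 0.45 at 10%, 0.490 × 1.32 = 0.65 at 20%, 0.576 × 1.32 = 0.76 at 30%.
- Lost: 55%, 35% and 24%.

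If both ICCs were equal, the ratio would be 1 and the Step 1 figures would return.

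**Step 3: illustrative power.** This is a t-test on school means with nine schools split four and five (7 df), without pair matching or baseline adjustment, at d = 0.5.
- Score: SE = √[(2.56 / 32.2) × (1/4 + 1/5)] = 0.189 SD. Noncentrality is 0.5 / 0.189 = 2.64 and power is 62%.
- Cut: the same shift moves the proportion from p₀ to p₁ = Φ(z_p − 0.5). SE = √{(1.94 / 32.2) × [p₀(1 − p₀)/4 + p₁(1 − p₁)/5]}, taking four control schools.

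| p₀ | p₁ | Noncentrality | Power |
|---|---|---|---|
| 0.10 | 0.037 | 1.48 | 25% |
| 0.20 | 0.090 | 1.89 | 37% |
| 0.30 | 0.153 | 2.14 | 46% |

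With five control schools instead, the range is about 27–48%. At d = 0.2, power is about 15% for the score and 9–12% for the cut.

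**The case against.** The strongest reply is that this is a condensed article. It calculates a named DSRS-C score and provides a model for continuous variables, so the full plan may analyse the score. A reader might infer that the score serves only to form the cut, or that the article expressly assigns the DSRS-C to logistic regression. It says neither. What stands is that the index is defined as the rate, and that no section names the score as an outcome.

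A reader might also infer that half or more of the information is lost. For independent children that holds only at about 21% prevalence or below. With the ICCs used here it holds only near 10%. Nor can one say that few children reach 16, or count cases per school, because the article gives no prevalence.

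The effect size is borrowed: section 2.7 illustrates d = 0.50 with stiffness index and MVPA, not depression. At smaller effects both analyses are weak, because nine schools are the main limit and changing the outcome scale does not remove it. A null result would therefore not become decisive.

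Finally, a rate from a validated scale with an established threshold is a legitimate measure, and easy to explain to schools and families. That is a good reason to keep reporting it. It does not require the rate to carry the test of effect.

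**Conclusion.** The point holds as a low-cost improvement to a secondary analysis. Defining the mental-health index by the cut gives up roughly 25–55% of the information under the clustered assumptions, and 42–66% if children are treated as independent or the two ICCs are equal, over an assumed prevalence of 10–30%. At d = 0.5 that means power of about 62% for the score against 25–46% for the cut.

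These sizes rest on a roughly normal score, an effect that shifts the whole distribution, the implied 290 children, the assumed prevalence and the assumed binary ICC. An effect confined to children near 16 would narrow or reverse the difference, but the article posits no such effect. The cost is precision, not bias, and neither primary outcome is touched. A reader might take the point as placing one of the trial's main hypotheses at risk. The introduction states a single broad hypothesis over physical, mental and social factors, and section 2.5.2 lists mental health as one of many secondary outcomes.

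**What to change.** In sections 2.6.5 and 2.10, name the July 2019 DSRS-C total score, adjusted for the July 2018 score, as the analysed mental-health outcome in the general linear mixed model already planned. Keep the proportion scoring 16 or more, by group, as a supportive summary. If the full analysis plan already does this, align the article's definition of the index with it.

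The cost is wording only: both scores are collected and the model is in the plan. The downside is that a difference in score points is less direct to read than a rate, which is why the rate stays in the report.

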#### 2.6.6. Social Health

The GRAPE study questionnaires included the following social health variables: attitude to PA, attitude to physical education (PE), behaviour change stage for PA, physical competence, school connectedness, personality traits, non-cognitive skills (grit, self-esteem, and self-control). 

The children’s attitude to PA and PE was determined using four responses (like, a little like, a little dislike, dislike) when asked whether they liked or disliked PA and PE classes. The behaviour change stage was assessed using the Transtheoretical Model of Change (TTM) proposed by Prochaska and Velicer [32]. Depending on the actual behaviour in the past and present and the readiness for that behaviour, the behaviour was divided into five stages: ‘precontemplation’, ‘contemplation’, ‘preparation’, ‘action’ and ‘maintenance’. Physical competence was evaluated using the Physical Competence Scale developed by Okazawa et al. [33]. This scale used 12 items to evaluate three factors: ‘physical competence’ (confidence to do physical exercise well); ‘feeling of control’ (confidence to do physical exercise well through effort and training), and ‘peer and teacher acceptance’ (recognition accepted by peers and teachers). School connectedness was measured using three items: ‘I like school’, ‘School is a nice place to be’, and ‘Sense of belonging at school’; the first item was answered using a four-point scale (like very much, like, dislike a little, dislike a lot) and the second two items were answered using five options (strongly agree, agree, neither agree or disagree, disagree, strongly disagree) [34]. The items were summed to create a composite score. Personality traits were assessed using a valid and reliable Japanese version of the Ten Item Personality Inventory (TIPI-J) [35]. The TIPI-J is a scale of the Big-Five personality dimensions: Extraversion, Conscientiousness, Agreeableness, Neuroticism, and Openness to experience. Each item was scored on a 1–7-point scale, and the scores were summed for each of the 5 dimensions.

##### Non-Cognitive Skills

As non-cognitive skills, grit, self-esteem and self-control were measured. Grit was assessed using the Japanese-translated version of the eight-item grit scale for children developed by Duckworth et al. [36]; the internal validity of the scale is confirmed by the authors [37]. The average value of the five options for the eight items was determined as a grit score (5: extreme grit, 1: lack of grit). Self-esteem was estimated using the Two-Item Self-Esteem scale (TISE). The TISE consists of two aspects of the self-esteem concept (self-evaluation and self-acceptance) and demonstrated concurrent validity by positive high correlations between the TISE and pre-existing self-esteem scales (i.e., Rosenberg’s self-esteem scale [38,39]). Self-control was evaluated by the Japanese-translated version of the Brief Self-Control Scale (BSCS-J) [40]. BSCS is a valid and reliable scale consisting of 13 items with responses that include five options ranging from ‘very much like me’ to ‘not like me at all’. As a parameter of family socioeconomic status, family affluence was measured using the family affluence scale, which has been validated in the European Health Behaviour in School-aged Children study [41] and is based on four questions: family car ownership; number of family trips per year; having one’s own bedroom; and total number of computers at home.

#### 2.6.7. Others

Other questions included undertaking non-sports lessons (such as cram schools; private tuition, yes/no), time spent on studies in a week (hours/week), knowledge of the effects of PA (five questions about the association between exercise, osteoporosis, cancer, memory, income and sedentary behaviour). 

### 2.7. Sample Size

The sample size was calculated based on the effect sizes (d = 0.50) derived from our previous study [29]; for example, the sample size was determined to detect a mean difference of five SI between the intervention and control groups with a standard deviation (SD) of 10 SI, and a mean difference in MVPA of 10 min/day with a SD of 20 min. A total of 63 children were required per group to detect a change in effect size with the alpha level set at 0.05 and power at 0.80.

To account for clustering, the required sample size of 63 children was adjusted by a design effect of 1 + (m − 1) ρ, where m is the average number of children per cluster and ρ is the intra class coefficient (ICC). We estimated that each school had 20 children and an ICC of 0.05. Using these estimates, the total required sample size was found to be 246 children (63 × (1 + (20 − 1) × 0.05 × 2 groups)). Furthermore, we assumed that 70% of the schools and 90% the children would accept participation, and 10% would drop-out during the study period. Therefore, it was assumed that at least 433 children were needed. Therefore, we recruited children from the 4th and 5th grade of all schools in Koshu City (13 schools, 511 children).

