### 2.8. Randomisation

Randomisation was conducted at the school level after baseline data were collected. This study was conducted in nine schools (18 classes, one class in each 4th and 5th grade; Figure 1). These schools were matched by size (total number of children) and region (Enzan or Katsunuma area) into four pairs. These pairs and one school with the smallest number of children in Koshu City were randomly assigned to either the intervention group or the control group using random numbers in Microsoft Excel by a researcher who was not directly involved in the implementation. The schools were each assigned a random number, and the school with odd last digits random number in each pair was assigned to the GRAPE intervention group. If the last digit was the same, GRAPE intervention group was assigned by the last second digits random number.

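### The design effect assumes 20 children per school, but the plan's own counts give about 39 (about 32 after planned losses), so 246, 433 and the 80% power do not hold as stated

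*Protocol article*

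**What the plan says.** Section 2.7 (Sample Size) starts from a standardised difference: "The sample size was calculated based on the effect sizes (d = 0.50) derived from our previous study". For bone stiffness it spells this out as "detect a mean difference of five SI between the intervention and control groups with a standard deviation (SD) of 10 SI". For the other primary outcome, MVPA, it takes 10 min/day against an SD of 20, which is the same standardised difference. The unadjusted result is 63 children in each arm, and the error rate and power behind it are given as "with the alpha level set at 0.05 and power at 0.80".

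The section then applies the design effect 1 + (m − 1)ρ, with m defined as the average number of children in a cluster, and fills it in: "We estimated that each school had 20 children and an ICC of 0.05". This yields 246 children. Allowing for 70% of schools and 90% of children taking part and 10% dropping out, it arrives at 433. The paragraph ends: "Therefore, we recruited children from the 4th and 5th grade of all schools in Koshu City (13 schools, 511 children".

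Section 2.8 (Randomisation) makes the school the unit of allocation and reports: "This study was conducted in nine schools (18 classes, one class in each 4th and 5th grade; Figure 1". Four pairs and one single school were allocated, so the split is 4 against 5.

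**The concern.** The cluster size drives the design effect, and the paragraph gives two incompatible values for it. If schools had 20 eligible children, 13 schools would hold 13 × 20 = 260, and the 433 children said to be needed could not be found there. The counts in the same paragraph give 511 / 13 = 39.3. Too small an m understates the design effect, and with it the number required.

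The calculation serves both primary outcomes. If the trial reports no significant difference, a reader who takes the stated power at face value will treat that as good evidence against an effect of 5 SI or 10 min/day. That inference is weaker than section 2.7 implies.

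**Working it through.** **Inputs (section 2.7 unless noted).** d = 0.50; alpha 0.05 (two-sided assumed, because it reproduces 63); power 0.80; ICC 0.05; m = 20; school uptake 0.70, child uptake 0.90, retention 0.90; 13 schools with 511 children. Nine schools randomised (section 2.8).

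**Step 1: the plan's figures reproduce from m = 20.**
- Per group: 2 × (1.96 + 0.8416)² / 0.5² = 62.8, so 63.
- Design effect: 1 + 19 × 0.05 = 1.95.
- Total: 63 × 1.95 × 2 = 245.7, so 246. (The printed bracket puts the factor 2 inside the design effect, which would give 182.7. This is a typesetting slip, since 246 needs the factor outside.)
- Invited: 245.7 / (0.7 × 0.9 × 0.9) = 245.7 / 0.567 = 433.3, so 433.

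The arithmetic is sound; one input is not.

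**Step 2: cluster size from the plan's own counts.**
- Eligible per school: 511 / 13 = 39.3.
- Analysed per school after planned losses: 39.3 × 0.9 × 0.9 = 31.8.
- Check on 20: nine schools of 20 give 180 children, below the 246 required.

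**Step 3: the plan's formula with m = 31.8.**
- Design effect: 1 + 30.8 × 0.05 = 2.54.
- Analysed: 63 × 2.54 × 2 = 320.
- Invited: 320 / 0.567 = about 564, more than 511.
- Conversely, 511 × 0.567 = 290 analysed, short of 320.

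**Step 4: power with nine schools, the plan's normal approximation.** 70% of 13 is 9.1, so nine schools is also what the plan expected. The standard error in SD units is √[DE × (1/(4m) + 1/(5m))], and power is Φ(0.5/SE − 1.96).

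| m analysed | Design effect | SE | 0.5/SE | Power |
|---|---|---|---|---|
| 20 (as stated) | 1.95 | 0.209 | 2.39 | 67% |
| 31.8 (planned losses) | 2.54 | 0.190 | 2.64 | 75% |
| 39.3 (no losses) | 2.915 | 0.183 | 2.74 | 78% |

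Power reaches 80% only at about 46 analysed children per school.

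**Step 5, a separate matter: nine clusters.** An unmatched comparison of nine schools has 9 − 2 = 7 degrees of freedom. Using the noncentral t with the same 0.5/SE:

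| m analysed | Power, 7 df | Detectable difference at 80% power |
|---|---|---|
| 20 | 54% | 0.68 SD |
| 31.8 | 62% | 0.62 SD = 6.2 SI or 12.4 min/day |
| 39.3 | 65% | 0.60 SD |

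**Step 6: sensitivity to the ICC at m = 31.8.**

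| ICC | Normal approximation | 7 df |
|---|---|---|
| 0.03 | 85.8% | 73.9% |
| 0.05 | 75.1% | 62.1% |
| 0.10 | 54.8% | 43.5% |

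**The case against.** **The cluster-size error is small by the plan's own method.** This stands. At nine schools the shortfall is about 5 points with planned losses and about 2 without. A reader might infer that the wrong m brings power down to 62%. The documents do not support that: the further fall comes from the t reference on 7 degrees of freedom. That is a different issue, and an analysis plan that is not shown may deal with it. The two figures should be kept apart.

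**The sizes of the nine schools are unknown.** Also true. Figure 1 is not shown, and section 2.8 says the nine include the city's smallest school. Carrying over the 13-school mean is an assumption. It does not rescue the paragraph, though: at ICC 0.05 smaller schools mean lower power, and if 20 were right for these nine they would supply only 180 children. In that case the design effect would be correct and the shortfall would lie in the number of children.

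**The ICC is itself a guess, and matching or baseline adjustment may help.** This stands as a limit on any single power figure. At ICC 0.03 the normal approximation exceeds 80%. Section 2.7 claims no gain from matching or baseline adjustment, so none is counted; a matched analysis would also change the degrees of freedom.

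**Two further readings go too far.** One could put m = 39.3 into the formula and then divide by 0.567, giving about 648 invited. That combines a cluster size without losses with an inflation for losses. Without child-level losses the divisor is 0.7, and 367 / 0.7 is about 524, only just above 511. One could also state as fact that 20 is a class size. Since 39.3 / 2 = 19.7 and each school has two classes this is plausible, but the article does not say so.

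**The Discussion concedes small clusters and too few participants.** It does, and that tempers over-reading. It neither corrects m nor withdraws the 80%.

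**Conclusion.** Wrong as written. Section 2.7 contradicts itself on the cluster size, and its 246, 433 and 80% rest on the value that its own counts rule out as an average over the 13 schools. On the plan's formula with m = 31.8, the requirement is 320 analysed and about 564 invited. With nine schools, power for 0.5 SD is about 75% by the plan's method (67% to 78% for m from 20 to 39.3).

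The small number of clusters is a second and larger cost: about 62% on 7 degrees of freedom (54% to 65% over the same range).

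These sizes assume the 13-school mean for the nine schools, an ICC of 0.05, and no gain from matching or baseline adjustment. The ICC matters more than m, so no single figure should be read as the trial's true power. The contradiction itself depends on none of these assumptions.

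**What to change.** In section 2.7:
- State that the planning value of 20 children per school is inconsistent with 511 children in 13 schools. Keep it on record as the assumption made at the time.
- Restate the design effect, the required numbers and the achieved power (or detectable difference) from the actual mean size of the nine schools. Until that is given, use m = 31.8 with the range above.
- Give the small-cluster figure on its own line, with its degrees of freedom and its sensitivity to the ICC.
- Remove the unqualified 80% power claim.

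Non-significant results should then be read from the confidence interval, against 5 SI and 10 min/day. The cost is one reworded paragraph and a less favourable statement of power. Nothing in the conduct of the trial changes, and no extra recruitment is needed.
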